## Methods

### Study design

This multi-center study examines the addition of two parental components to a TF-CBT-based treatment for children exposed to IPV, which results in a 2 (preparatory program present versus absent) x 2 (parent-child interaction present versus absent) factorial randomized experimental component trial. The study includes pre-treatment (T1), treatment, post-treatment (T2), and a 6-month follow-up (T3) assessment, and will include 100 children and their custodial parents (Fig. 1 depicts the study design). The baseline assessment (T1, see Fig. 2) will take place one week prior to the start of the 6-week preparatory program. To ensure comparability across treatment conditions, in the “No preparatory program” condition, parents and children will be assessed 7 weeks before the beginning of the TF-CBT-based treatment. Additionally, parents and children will be assessed three times during treatment, namely at the beginning of the intervention (session 1), after sharing the trauma narrative of the child with the parent (session 9), and at the end of the intervention (session 15). These measurements allow us to test mediating pathways [47], and allow us to monitor, and if necessary control for, new IPV or other stressful incidents. The second assessment (T2) will take place one week after the last session of the TF-CBT-based treatment for all four conditions. The third assessment (T3) will be at a follow-up, six months after the last session of the treatment. Regardless of condition, all participants receive the standard TF-CBT-based treatment. The difference lies in the addition of the two parental components. Families who are assigned to “No preparatory program“ or “No parent-child interaction” conditions will not receive an alternative component additionally to standard TF-CBT based treatment.

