### Randomization, blinding, and treatment allocation

Recruitment will take place in three mental health centers in The Netherlands. For each center families are referred for treatment after children have been exposed to interparental violence. As soon as a group of approximately 8 families have met the inclusion criteria for participation in the HORIZON group treatment (see Inclusion and Exclusion Criteria), and after informed consent is obtained, the families participating in the study will participate in T1 measurements. Parents and children are asked to fill out questionnaires and to participate in two observational tasks. Additionally, the parent is interviewed about the observational tasks. After T1, the group will be randomly assigned to one of the four treatment conditions (see Fig. 1) by an independent researcher using a randomization procedure with lottery drawings. Conditions 1 & 2 will start one week after T1, and conditions 3 & 4 will start seven weeks after T1. One week (T2) and six months (T3) after the end of the program, parents and children are again invited to fill out questionnaires (see Fig. 2). At all assessments the teacher is also sent a questionnaire. Typically, the intervention group consists of two child groups (4–7 years and 8–12 years, respectively) and one parent group. Usually there is only one parent group, because families often have more than one child who participate in the intervention, and because parents without visitation rights do not participate. The child groups receive treatment at the same time but in different rooms. The parents of children in both groups receive group sessions on the same time. Because it is not feasible for participating trauma centers to start four interventions at the same time, we cannot randomly assign individual children or parents to one of the four conditions. Therefore, we choose randomization by group just before the start of the group therapy and after T1. Parents and children are blind to treatment condition until randomization is carried out just before the (preparatory) program starts. Clinicians will be blind for treatment condition until all families are indicated for treatment. The assessments include videotaped observational tasks. Independent research assistants will code these videos. All coders are blind for treatment condition. Sometimes it will take a few months before families can participate in one of the four group interventions, due to waiting lists and enrollment numbers to form treatment groups. If necessary, parents and children will receive family or individual stabilization intervention during this time. Independent of their experiences with treatment preceding participation in the HORIZON, all participating families will be measured at T1 at the same time to ensure comparability of the families in the study.

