### Statistical analyses and sample size calculation

All variables are measured on at least an ordinal scale. All scale scores will be examined for normality. Should we observe deviations, steps will be taken to ensure optimal estimation of parameters in our analyses. The proposed study includes a nested structure, because individuals are treated within groups. Following the recommendations by Peugh [118], we will calculate design effects to assess group-level dependency and examine whether multi-level modeling is required. To ensure comparability of the randomized conditions, we will control for duration and severity of the IPV [45], parental psychopathology [46], and new incidents of IPV. Power calculations were performed using the program G*power 3 [119], assuming that individual-level effects can be treated as independent data. We determine required sample size to be 100 parent-child dyads, achieving statistical power of at least .80 for the primary and secondary objectives, as described in more detail in the following paragraphs. We will test for the randomness of missing data. If this is the case we will use multiple imputation.

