### Primary objective

The first goal of the present study is to examine the efficacy of two parental components that complement a TF-CBT-based core treatment for children who have been exposed to IPV. Therefore, a multiple regression analysis will be executed with two dummy variables as independent variables, representing both parental components (dummy 1 = parent preparatory program present vs. absent; dummy 2 = parent-child interaction sessions present vs. absent) and their interaction. Dependent variables are child symptoms (primary outcomes) at the three time points (T1, T2, and T3) clustered into 1) Trauma symptoms, 2) Internalizing symptoms, 3) Externalizing symptoms. Analyses will be independently executed for the three dependent variables. Because children in each group receive intervention, a medium effect size is expected (f^2^ = .15). With a maximum of five predictors and an alpha of .05, we achieve a power of .84 with 100 children included in the study.

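### The primary regression treats the pre-randomisation T1 symptom score as a dependent variable and never as a baseline covariate, which costs precision and leaves T2 and T3 exposed to chance imbalance

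*Protocol article*

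**What the plan says.** Under Primary objective in the statistical section, the article specifies that "a multiple regression analysis will be executed with two dummy variables as independent variables, representing both parental components", together with their interaction. It continues: "Dependent variables are child symptoms (primary outcomes) at the three time points (T1, T2, and T3"), grouped into trauma, internalizing and externalizing symptoms. It adds that "Analyses will be independently executed for the three dependent variables".

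The timing of T1 is clear. Study design says: "The baseline assessment (T1, see Fig. 2) will take place one week prior to the start of the 6-week preparatory program". Randomization, blinding, and treatment allocation says: "After T1, the group will be randomly assigned to one of the four treatment conditions".

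The adjustment variables are given under Statistical analyses and sample size calculation: "we will control for duration and severity of the IPV [45], parental psychopathology [46], and new incidents of IPV". The child's T1 symptom score is not among them.

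The power statement is: "With a maximum of five predictors and an alpha of .05, we achieve a power of .84 with 100 children included in the study". Symptom scores from T1 and later waves are linked explicitly only in the exploratory cross-lagged models.

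**The concern.** A score taken before allocation cannot be affected by allocation. Listing it as an outcome of the component dummies, with nothing in the model to separate the time points, gives it a role in which it carries no information about treatment. The role in which it would help, as baseline covariate for the same measure at T2 and T3, is not assigned to it.

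Two things are at stake in the primary analysis. The first is precision: a child's earlier score on a scale usually predicts the later score, and the T1 data are collected anyway. The second is protection against chance imbalance. Whole therapy groups are randomised, and few of them, so the conditions can easily differ at baseline on the outcome itself. The plan controls for other variables expressly to make the conditions comparable, but not for the most direct measure of comparability on the primary outcome.

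**Working it through.** **1. The plan's own figure.** Inputs from Primary objective: f² = .15, five predictors, alpha .05, N = 100. For the overall regression F test, the noncentrality is .15 × 100 = 15 with 5 and 94 degrees of freedom. Power is .843, so the stated .84 is reproduced. It is an overall test on one outcome value per child, with no repeated-measures structure.

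**2. Is there room for T1 in the stated model?** Two dummies and one interaction make three terms. A maximum of five predictors leaves two places. Nothing assigns either to T1, and the listed controls (duration and severity of violence, parental psychopathology, new incidents) would fill or exceed them.

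**3. What T1 adjustment would gain.** The article gives neither a standardised component difference d nor a T1-to-follow-up correlation r, so both are assumed: d = 0.5, r = .3 to .7. Further assumptions are 50 versus 50 children for one component, independent children, no dropout and two-sided alpha .05.

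- Standard error in SD units: √(v × 4/100), with v = 1 without T1 and v = 1 − r² with T1 as covariate.
- Noncentrality: 0.5 / standard error. Degrees of freedom: 96 without T1, 95 with it. Power is from the noncentral t distribution.
- Equivalent unadjusted N: 100/(1 − r²).

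| Analysis | v | SE | Noncentrality | Power | Equivalent N |
|---|---|---|---|---|---|
| Without T1 | 1.00 | .200 | 2.50 | .70 | 100 |
| T1 covariate, r = .3 | .91 | .191 | 2.62 | .74 | 110 |
| T1 covariate, r = .5 | .75 | .173 | 2.89 | .82 | 133 |
| T1 covariate, r = .6 | .64 | .160 | 3.13 | .87 | 156 |
| T1 covariate, r = .7 | .51 | .143 | 3.50 | .93 | 196 |

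With d = 0.4 the pattern is the same: .51 without T1, against .55, .63, .70 and .79 with it.

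**4. How likely is chance imbalance?** Groups form at approximately 8 families, so 100/8 = 12.5, or about 12 randomised units at one child per family, and fewer if siblings take part. For one component, the standard error of the baseline difference is √(4/100) = .20 SD if the intraclass correlation is 0. At an assumed intraclass correlation of .10 with 8 children per group, the design effect is 1 + 7 × .10 = 1.7 and the standard error is .20 × √1.7 = .26 SD. The chance of a difference of at least 0.3 SD in either direction is then about 13% (0.3/.20 = 1.50) or 25% (0.3/.26 = 1.15) per outcome and component. Without adjustment, a 0.3 SD baseline difference shifts the follow-up comparison by about r × 0.3: .09 SD at r = .3, .15 SD at r = .5 and .21 SD at r = .7.

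**The case against.** The strongest reply is that nothing invalid has been specified. Groups are randomised, so a regression of T2 or T3 symptoms on the component terms estimates the component effect without bias. The primary objective is the effect on child symptoms, which such a regression addresses. This stands. A reader might infer that the model cannot answer the trial's question about improvement, but the article does not support that. The loss is in precision and in protection against imbalance.

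A second reply is that listing three time points may be shorthand for a longitudinal model, in which T1 may properly sit among the outcomes. That is possible, and T1 as an outcome is not wrong in itself. But such a model needs time and time-by-component terms, and the article describes a multiple regression with neither.

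A reader might also infer that T1 dilutes the estimated effect. That would happen only if the three time points were stacked with no time term: (0 + 0.5 + 0.5)/3 = 0.33 SD instead of 0.5. The article does not say that they are stacked, and a power calculation on one value per child fits separate regressions better.

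Third, the size of the gain rests on assumed inputs. At r = .3 it is small. If the article's f² = .15 were read as the effect of one balanced component, d would be 2 × √.15 = .77 and unadjusted power already about .97, leaving little to gain. With allocation by group, the gain also depends on how much T1 explains of the variation between groups, which is unknown. All of this stands, so the figures compare analyses and do not give this trial's power.

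Finally, three outcomes analysed separately, with no single primary time point, may suggest a multiplicity fault. That is a separate and debatable question, commonly left to a fuller plan. It forms no part of this point.

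**Conclusion.** The point holds as a weakness in how the primary model is specified. The article lists a pre-randomisation score as a dependent variable, names no term that separates the time points, and leaves that score out of the covariates it does name. A component effect at T1 is zero by design. The T2 and T3 comparisons are unbiased but less precise than they could be, and they are open to chance imbalance with about 12 randomised groups.

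In terms of power, the gain from adjustment runs from slight (.70 to .74 at r = .3) to large (.70 to .93 at r = .7). This assumes d = 0.5, 100 independent children and no dropout. Clustering makes all the absolute values optimistic. That T1 would be the strongest available covariate is a reasonable expectation, but the article does not show it.

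**What to change.** For each primary outcome, state one of two models:

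- **Covariate model.** T2 and T3 scores are the outcomes, with the T1 score of the same measure as covariate beside the two component terms and their interaction. T1 is then no longer a dependent variable.
- **Longitudinal model.** T1, T2 and T3 all stay in the outcome vector, with baseline means constrained equal across conditions and explicit time and time-by-component terms.

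These are alternatives: T1 leaves the outcomes under the first and stays under the second. A plain change score is not a substitute. Its variance factor is 2(1 − r), and under the same assumptions its power is .55 at r = .3 and .70 at r = .5, no better than ignoring T1.

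Under the covariate model, count the T1 score among the predictors. Under either model, restate the power for the model chosen, giving the assumed correlation and its source. The cost is one degree of freedom for the covariate and a redone power statement. No new data are needed, because T1 is already collected from every family in the study.

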### Primary objectives

The primary objective of the present study is to examine the efficacy of two parental components that complement a TF-CBT-based core treatment for children who have been exposed to IPV. Specifically, the study involves a randomized controlled trial with a 2 (parent preparatory program present vs. absent) X 2 (parent-child interaction sessions present vs. absent) factorial design to evaluate the effects of these two parental treatment components on child symptoms.

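### The power of .84 given for the primary objective belongs to an overall five-predictor F test, not to the test of either parental component or of their interaction

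*Protocol article*

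**What the plan says.** The Primary objectives section of the protocol article sets up a 2 × 2 factorial trial "to evaluate the effects of these two parental treatment components on child symptoms", and Trial objectives says that independent and combined effects will be examined.

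Under Primary objective in the statistical section, the model is a multiple regression with "two dummy variables as independent variables, representing both parental components" and their interaction, run separately for trauma, internalizing and externalizing symptoms. The effect size is justified in one sentence: "Because children in each group receive intervention, a medium effect size is expected (f^2^ = .15"). The power statement follows: "With a maximum of five predictors and an alpha of .05, we achieve a power of .84 with 100 children included in the study".

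The general section, Statistical analyses and sample size calculation, rests the sample size on this and the secondary calculations: "We determine required sample size to be 100 parent-child dyads, achieving statistical power of at least .80 for the primary and secondary objectives". It names G*Power 3, treats individual children as independent, and lists control variables: duration and severity of the violence, parental psychopathology and new incidents.

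The protocol does not say which test the .84 refers to, which five predictors are meant, or whether f² = .15 is the effect of one component, of both, or of the whole model.

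**The concern.** A power figure is informative only for the hypothesis it was computed for. Here the hypotheses of interest are the effect of the preparatory program, the effect of the parent-child sessions, and their interaction. Each is a single coefficient or contrast. The stated inputs point instead to a test of the whole model. That test asks whether anything among five predictors explains symptoms, and at most three of the five are treatment terms.

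The sample size of 100 is presented as adequate for the primary objective on the strength of this figure. If a component shows no significant effect, readers will take it that the trial had .84 power to find one, which the calculation does not show.

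**Working it through.** **Inputs.** From Primary objective: f² = .15, at most five predictors, alpha = .05, N = 100, stated power .84. From Statistical analyses and sample size calculation: independent observations, G*Power 3. My assumption: equal cells of 25 children.

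**Formula.** For fixed-model linear regression with p predictors and a test of u of them, the statistic is noncentral F with u and v = N − p − 1 degrees of freedom and noncentrality λ = N × f². With p = 5, v = 94.

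**Step 1: reproduce .84.** With f² = .15, λ = 100 × .15 = 15.

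| Terms tested, of five in the model | Power |
|---|---|
| 5 (overall test) | .843 |
| 4 | .873 |
| 3 | .905 |
| 2 | .937 |
| 1 | .969 |

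Only the overall test gives .84. The figures under Secondary objectives follow the same convention: four predictors at f² = .15 give .874 (stated .87), and two predictors at f² = .10 give .803 (stated .80). The identification is therefore secure, and the arithmetic itself is correct.

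**Step 2: what that test can detect.** Two dummies plus one interaction are three terms. The other two of the five predictors must be something other than treatment. The overall test depends only on total λ, whichever predictors supply it. If the non-treatment predictors carry all of f² = .15 and both components do nothing, λ is still 15 and the test still rejects with probability .84.

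**Step 3: power of the test of one component** (u = 1, v = 94). The result depends on how much of f² belongs to that component.

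| Allocation of f² = .15 | Component f² | λ | Power |
|---|---|---|---|
| All to one component | .15 | 15 | .97 |
| Shared over 2 terms | .075 | 7.5 | .77 |
| Shared over 3 terms | .05 | 5 | .60 |
| Shared over 5 terms | .03 | 3 | .40 |

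Power of .80 needs a component f² of about .08.

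**Step 4: the same in standard deviation units.** In a balanced design a main effect of d residual standard deviations has f² = d²/4. So f² = .15 on one component means d = 2√.15 ≈ 0.77, and power of .80 needs d = 2√.08 ≈ 0.57. An effect of 0.5 SD (my assumption; the protocol gives no such figure) has f² = .0625, λ = 6.25 and power .70.

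If 0.5 SD is measured before covariate adjustment and the covariates explain a share R² of the within-cell variance, λ becomes 6.25/(1 − R²). At R² = .20, λ = 7.81 and power is .79. At R² = .25, λ = 8.33 and power is .82. The protocol does not give R².

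**Step 5: interaction and coding, at 0.5 SD with R² = 0.**
- Interaction (a difference of 0.5 SD between the two simple effects): variance 4/25, λ = .25 × 25/4 = 1.56, power .24.
- If the dummies are coded 0/1 with the interaction in the model, each dummy coefficient compares 25 with 25 children in the absence of the other component: λ = .25 × 25/2 = 3.125, power .42, against .70 for the main effect.

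**The case against.** The strongest reply is that the protocol's only definition of a medium effect is f² = .15. If that is meant as the effect of one component, power for its main effect is .97, so .84 understates it. This stands as a possible reading, and it is why a reader should not infer that the trial is underpowered. Nothing in the protocol fixes the component effect at 0.5 SD or splits f² across terms. Even at 0.5 SD, the .70 assumes that covariates explain nothing, and it passes .80 once they explain about 25% of the variance.

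The reading is demanding, though. It implies a difference of about 0.77 SD from adding one component to a treatment that every child receives, and the protocol gives that shared treatment as its reason for expecting only a medium effect.

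A second reply is that the protocol never proposes to conclude efficacy from the overall F test. That is right. The rejection rate in Step 2 shows what the .84 measures; it is not a planned decision error. But it confirms that the power was computed for a test the analysis does not use to answer the primary question.

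A third reply is that coding is a detail an article may leave to the full plan, and that average effects can be obtained from the same model under any coding. Also right: the article says only that the dummies represent present versus absent, so a reader cannot conclude that the factorial advantage has been lost. The coding remark is a caution and does not carry the point.

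**Conclusion.** The point holds as a misstatement of what the power figure refers to. The .84 is the power of the overall five-degree-of-freedom test. It is not the power for either component or for the interaction, and the protocol gives no figure for those. The arithmetic is sound; the hypothesis is the wrong one.

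The direction of the error is not determined. Component power runs from .40 to .97 over the allocations shown, and .84 corresponds to none of them. The general statement of "achieving statistical power of at least .80 for the primary and secondary objectives" is therefore unsupported for the primary objective as worded, though not shown to be false.

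All component figures assume 100 independent children, equal cells, five predictors in the model and alpha = .05. The trial randomizes whole therapy groups, so independence is itself an assumption; its effect on power is a separate matter and is not counted here.

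**What to change.** - In Primary objective, state the effect assumed for one component, in f² or SD units, and its basis. Replace the .84 with the power of the one-degree-of-freedom test of each component's main effect and of the interaction at that effect.
- In Statistical analyses and sample size calculation, limit the claim of at least .80 to the tests for which those figures support it.
- State that each component's effect is estimated averaged over the other factor, for example with −0.5/+0.5 coding, so that a 0/1 dummy coefficient is not read as the main effect.
- Present any illustrative figure, such as .70 for a main effect or .24 for an interaction at 0.5 SD, as conditional on the assumed effect, on the covariate R² and on independence of children.

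The cost is a recalculation and a few sentences; no additional children or data are needed. The restated power may be higher or lower than .84, depending on the component effect that the investigators can justify.
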